### Adverse events

The occurrence of adverse events will be monitored, including muscle stiffness, soreness, falls, or injuries resulting from the intervention. An Adverse Event Form will be completed by YMCA staff.

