#### Intervention group: FIT for FUNCTION

The 12-week FIT for FUNCTION program comprises an exercise component (2×/week group classes, 1×/week independent exercise) and a self-management / education component (1×/week).Exercise: group exercise sessions (60 min, 2×/week) will be delivered by a kinesiologist trained to work with individuals with stroke. A stroke rehabilitation physiotherapist will provide on-site consultation 4 h per week and remote consultation 3 h per week. These group classes were adapted from the Community-Based Exercise Program for Persons Living with Stroke [56] and a DVD training package was developed for staff as a standardized competency-based approach. The exercise classes comprise: (i) warm up (10 min); (ii) task-oriented strengthening and cardiovascular conditioning (20 min); (iii) mobility and balance (20 min); and (iv) cool down (10 min). The feasibility of this program was established in the pilot study, with no adverse events and four participants (6.6%) withdrawing from the program (one related to the intervention and three unrelated to the intervention). From the pilot study, we found that maintaining a class size of 12 and a staff:participant ratio of 1:4 was important for ensuring safety of all participants. See Additional file 4 for a detailed description of the exercise program.

Of note, the cardiovascular conditioning component will be enhanced in this proposed trial. Individualized prescriptions will be determined using HR reserve and rating of perceived exertion methods that we have used extensively in previous stroke trials [37, 39]. Participants will also attend an independent exercise session (1×/week), where they will have full access to equipment and facilities at the YMCA.

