For all exercise sessions, duration (time) and intensity (HR, rating of perceived exertion) will be recorded.2.Self-management and education. LWS is an eight-session group self-management education program facilitated by a LWS-trained YMCA staff member, with the option of utilizing a stroke survivor as a co-facilitator. These sessions are held 1×/week and help stroke survivors and their caregivers cope with stroke related changes and engage as active participants in the management of their care. A self-management problem-solving approach is used to develop self-efficacy. Topics include: understanding stroke; physical changes and challenges; swallowing and nutrition; cognition, perception, and communication; emotions; focusing on depression; activities and relationships; reducing the risk of stroke; and moving forward.

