#### Control group: standard YMCA membership

The control group will receive a 12-week complimentary YMCA membership and the frequency of attendance to engage in exercise will be self-determined. As part of this membership, participants will have access to eight fitness coaching sessions to receive instruction about the use of equipment or exercise regimes. These coaching sessions will be provided by YMCA staff who we will train to work with individuals with stroke but are not involved in the FIT for FUNCTION program. The standard YMCA membership was chosen as the control intervention since it reflects what is currently available as an option for people with stroke wanting to participate in community-based exercise programming in the region.

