### Assessments

Before the initial assessment, the assessor will obtain written consent from each participant. Data will be entered directly into the database at the time of assessment using a tablet with a remote connection to REDCap, a secure web-based data management system. All assessments will take place at the YMCA with a physiotherapist trained in the administration of the outcome measures and in the use of REDCap.

Results from the pilot study confirm that the assessment sessions took approximately 90 min per participant and the sessions were generally well tolerated. At baseline, participant demographics will be recorded, along with stroke severity (NIH Stroke Scale), stage of recovery (Chedoke-McMaster Stroke Assessment), and co-morbidity and illness severity (Cumulative Illness Rating Scale) [57]. Cognitive impairment (MoCA) [58], presence of depressive symptoms (Centre for Epidemiologic Studies Depression Scale) [59, 60], and self-reported falls will be documented at baseline, 12 weeks, and 24 weeks along with the assessment of the primary and secondary outcomes (Fig. 2).

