### Data monitoring and auditing

This trial will not have a data monitoring committee and the study investigators will provide the auditing of the study since the estimated risk to the patients is low. The participants who undertake the research will be cleared to participate by a physician and determined to be medically stable and not at a high risk of mortality. The intervention of exercise and self-management and education have been studied with no serious adverse effects, so it is not expected that the participants will encounter any harm as a result of the intervention or control arm of the trial. There are no stopping rules or preliminary analyses planned.

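### Adverse events are recorded on a form that depends on YMCA staff contact, which differs by arm, so counts of stiffness, soreness and non-fall injuries are likely to be biased upward in the programme arm

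*Protocol article*

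**What the plan says.** The Adverse events section consists of two sentences. The first sets the scope: "The occurrence of adverse events will be monitored, including muscle stiffness, soreness, falls, or injuries resulting from the intervention". The second names the recorder: "An Adverse Event Form will be completed by YMCA staff".

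Other sections determine how often staff meet participants.

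- **Programme arm** (Intervention group: FIT for FUNCTION). Two staff-led group classes and one independent exercise session a week for 12 weeks. In addition, "LWS is an eight-session group self-management education program facilitated by a LWS-trained YMCA staff member".
- **Control arm** (Control group: standard YMCA membership). A 12-week membership in which "the frequency of attendance to engage in exercise will be self-determined", with access to eight coaching sessions.
- **Both arms** (Interventions). Attendance, resting blood pressure and a safety checklist at each exercise session.
- **Staff** (Contamination). The YMCA staff who deal with the intervention group have no contact with the control group.

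Two other sources cover part of the ground in both arms. Under Assessments, "self-reported falls will be documented at baseline, 12 weeks, and 24 weeks". Under Healthcare utilization and costs, a case report form built for the economic evaluation collects emergency visits, hospitalization and physician visits over 24 weeks.

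**The concern.** An adverse event reaches the form only if a member of YMCA staff learns of it. Staff meet programme participants on a fixed timetable and meet controls only when controls choose to come. A control who strains a muscle and stays away generates no checklist and no form. A programme participant with the same strain is due in class within days.

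The people who fill in the form also differ between arms and know the allocation. They are asked, at least for injuries, whether the event resulted from the intervention. That question has no obvious meaning for someone who was given a self-directed membership.

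At stake is the by-arm safety table. The article intends a positive result to support provincial and national roll-out, so readers will look at harms by arm. An apparent excess of soreness or injury in the programme arm could reflect closer observation and nothing else. Events in weeks 12 to 24 could be missed in both arms. No analysis can recover events that were never collected.

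**Working it through.** The article gives no adverse event rate and no contact ratio, so there is no figure to reproduce. The check has three steps.

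**1. Scheduled contact over 12 weeks**

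- Programme, staff-led: 2 × 12 = 24 classes, plus 8 education sessions = 32.
- Programme, independent exercise: 1 × 12 = 12, giving 32 + 12 = 44 sessions in all.
- Control, coached: at most 8, and optional.
- Ratio of staff-led contacts: 32/8 = 4.0. With the independent sessions included: 44/8 = 5.5.

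The checklist before each exercise session narrows this gap, because it applies at every control visit as well. Programme checklist contacts number 24 + 12 = 36. For v control visits a week the ratio is 36/(12v):

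| Control visits a week (assumed) | Control contacts | Ratio |
|---|---|---|
| 3 | 36 | 1.0 |
| 2 | 24 | 1.5 |
| 1 | 12 | 3.0 |
| 0.5 | 6 | 6.0 |

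**2. From contacts to recorded events**

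Assume that an event is recorded only if a session falls within the following 7 days, and that control visits occur at random times. Capture is then 1 − exp(−v). Two versions of the programme arm are shown: (a) random contact at three a week, capture 1 − exp(−3) = 0.950; (b) full attendance at fixed classes at least twice a week, capture 1.00. With equal true rates, the apparent ratio is programme capture divided by control capture.

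| Control visits a week | Control capture | Ratio (a) | Ratio (b) |
|---|---|---|---|
| 3 | 0.950 | 1.00 | 1.05 |
| 2 | 0.865 | 1.10 | 1.16 |
| 1 | 0.632 | 1.50 | 1.58 |
| 0.5 | 0.393 | 2.42 | 2.54 |

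If control visits were evenly spaced, a weekly visit would capture everything (ratio 1.0 against full programme capture) and a fortnightly visit 7/14 = 0.50 (ratio 2.0). The range is therefore about 1.0 to 2.5, governed by control attendance.

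To put this in counts, take 108 per arm, a true proportion of 20% in both arms and programme capture of 90% (all assumed apart from 108). The programme arm records 108 × 0.20 × 0.90 = 19.4 participants with an event. Control capture of 60% gives 108 × 0.20 × 0.60 = 13.0 (ratio 1.5), and 45% gives 9.7 (ratio 2.0).

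**3. Which events have an equal route**

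| Event | Route that is the same in both arms |
|---|---|
| Falls | Yes: self-report at baseline, 12 and 24 weeks, with no attribution |
| Events leading to emergency or hospital care | Partly: the costing form over 24 weeks, with no safety use stated |
| Stiffness, soreness, non-fall injuries | None described |
| These same events in weeks 12 to 24 | No staff session scheduled in either arm |

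**The case against.** The case on the other side has real substance.

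- **YMCA staff are not the only source.** A reader might infer from the Adverse events section that they are. Falls are self-reported at the scheduled assessments, and emergency and hospital use is collected to week 24. This stands, and it confines the problem to stiffness, soreness and non-fall injuries. The costing form fills the rest only in part: it exists for costing, and its reference to stroke may narrow what it collects.
- **Attribution may not be required.** It is tempting to read the section as recording only events caused by the intervention. The list is introduced as inclusive, and in "muscle stiffness, soreness, falls, or injuries resulting from the intervention" the qualifier may belong to injuries alone. The stronger reading is not established. On the weaker one, attribution still governs injuries.
- **An excess in the programme arm is not certain.** Controls receive the same checklist at each exercise visit, so a control who attends three times a week is seen as often for exercise as a programme participant. This stands: the lower end of the range is no bias. The direction remains likely, because the Discussion itself expects that controls may find it harder to adhere.
- **No between-arm safety test is planned.** Neither the objectives nor Table 2 contains one. This stands, so no false-positive rate is claimed. Any tabulation by arm would still carry the bias.
- **The article is a summary.** The content and timing of the form may be in the full protocol, and their absence is no finding. The point rests on what the article does fix: who completes the form, and how often those people meet each arm.
- **The missing monitoring committee is beside the point.** "This trial will not have a data monitoring committee" might look like an aggravating factor, but a committee would not correct unequal ascertainment.

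**Conclusion.** The point holds in a limited form. As written, the Adverse Event Form relies on staff who know the allocation, serve separate arms and have at least four times as many scheduled staff-led contacts with the programme arm (32 against at most 8). Recorded stiffness, soreness and non-fall injuries are likely to be biased upward in that arm relative to control, and events after week 12 have no described trigger in either arm.

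The size cannot be fixed from the article. Under an assumed 7-day capture window, equal true rates would appear as a ratio of about 1.0 at three control visits a week, about 1.5 at one a week and roughly 2.5 at one a fortnight. Attendance is recorded in both arms, so the actual imbalance in contact will be known afterwards. That would describe the bias but not restore the missing events.

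The documents do not support saying that the trial has no valid safety data, or that equal harm must look like excess harm. The primary outcome is not affected. The change is worth making because it is cheap and cannot be made retrospectively.

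**What to change.** Beside the existing falls question at 12 and 24 weeks, add one short fixed checklist for every participant in both arms, regardless of attributed cause. It should cover non-fall injuries, musculoskeletal pain or soreness, and cardiovascular events since the last assessment.

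Have participants complete it themselves, or have unblinded coordinating staff collect it. Asking it last at week 12 is not enough: if the same assessor returns, an answer that mentions a class injury could unblind the 24-week primary outcome.

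State that any safety tabulation by arm will use this checklist, the falls question and the emergency and hospital data from the costing form. Report the YMCA staff forms separately as session-related events, with attendance by arm beside them.

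The cost is a few minutes at visits that already take place, one REDCap form and an amendment by the route under Protocol modifications. Three limits remain. A small unblinding risk persists. Participants know their allocation, so self-report can still differ somewhat by arm. Recruitment has already begun, so the checklist will cover only assessments made after the amendment, and the tabulation should say so.

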### Sample size justification

The sample size calculation is based on the test of the null hypothesis that the mean reductions in RNLI scores in the two populations (intervention and control) are equal. The primary measure of effect is the change in RNLI scores from baseline to 12 weeks (two-tailed type I error of 0.05; type II error of 80%). The criterion for significance (alpha) has been set at 0.05. The test is two-tailed, which means that an effect in either direction will be interpreted. The sample size of 105 per group was calculated using an a priori sample size calculator for Student’s t-tests [91]. With the proposed sample size of 105 in each of the two groups (i.e. assuming a 1:1 allocation ratio), the study will have power of 80% to yield a statistically significant result using a t-test (assuming an intention-to-treat principle for the analysis) of the difference between mean changes in RNLI scores (12 weeks to baseline) at alpha = 0.05. This computation assumes that RNLI change scores are normally distributed, the mean difference is 3.1 (95% confidence interval [CI] = -3.37–9.56) (corresponding to mean changes of 6.26 [for the intervention group] vs 3.16 [for the control group]) and the common within-group standard deviation is 3.23 These estimates are modified estimates from our pilot trial, which account for the type of intervention planned for in this study. We calculated the sample size to address the primary outcomes. Table 1 provides the sample sizes for different values of the expected plausible difference and standard deviations.

**Table 1 Tab1:** Sample sizes for different plausible values of the mean difference and corresponding standard deviations

SD	1.0	2.0	3.0	4.0
3.0	292	76	38	20
4.0	506	128	60	24
5.0	788	200	90	52
6.0	1230	352	128	74
7.0	1604	404	182	100
8.0	1806	506	220	128
9.0	2598	652	292	200

Fixed α = 0.02 B = 0.05

To allow for subgroup analysis, and to control for factors of age and function, as well as balancing of the number of participants between the groups at the three sites, we chose a sample size of n = 182 (i.e. 91/group), which corresponds to a minimal clinically important difference of 3. This difference was selected because it is plausible and feasible to achieve as shown by our pilot study, and it is associated with a three-point clinically important improvement [92]. This sample size (91/group) would also provide 80% power to detect time by treatment interaction. Thus, with 30 participants per group for each of the three sites, and to account for dropouts (20%), the planned total sample size is (30 × 3 sites) (20%) × 2 groups = 216 participants, or 108 participants per group.

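### The printed SD of 3.23 cannot yield 105 per group (it needs 19), and the pilot interval shows that it is most likely a standard error; the SD behind the sample size is unstated

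*Protocol article*

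**What the plan says.** All of this stands in the protocol article under Sample size justification, unless noted.

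- Error rates: "two-tailed type I error of 0.05; type II error of 80" per cent. The second figure is evidently meant as power, because the section goes on to say that "the study will have power of 80% to yield a statistically significant result using a t-test".
- Effect: "the mean difference is 3.1 (95% confidence interval [CI] = -3.37–9.56"), from mean changes of 6.26 and 3.16.
- Variability: "the common within-group standard deviation is 3.23".
- Size: "With the proposed sample size of 105 in each of the two groups".
- Source: "These estimates are modified estimates from our pilot trial, which account for the type of intervention planned for in this study". The modification is not described.
- The next paragraph chooses 182 participants (91 per group) for a clinically important difference of 3, says of that difference that "it is plausible and feasible to achieve as shown by our pilot study", and arrives at 216 (108 per group) with 20% dropout.
- Table 1 covers SDs from 3 to 9. Its entry for SD 7 and difference 3 is 182.
- Pilot numbers: 61 participants (Background), split 33 and 28, of whom 31 and 24 had complete 12-week data (Missing data).

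**The concern.** A difference of 3.1 against an SD of 3.23 is a standardised effect of almost 1, which does not call for 105 per group. Nor can a pilot of 61 people with an SD of 3.23 produce an interval nearly 13 points wide. So the SD, the sample size and the interval cannot all describe the same calculation.

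This is the power claim for the primary outcome. If the SD that was really used is wrong or unsupported, readers cannot tell whether the trial can detect the 3-point difference on which it was sized, and a non-significant result would be hard to interpret.

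**Working it through.** **1. The plan's own calculation.** Inputs: difference 3.1, SD 3.23, two-sided alpha 0.05, power 80%. Standardised effect = 3.1 / 3.23 = 0.96. The exact two-sample t-test solves at 18.05, so 19 per group. Other settings (normal approximation) do not reach 105: one-sided 0.05 gives 14, alpha 0.02 gives 22, power 95% gives 29, and alpha 0.02 with power 95% gives 35. With SD 3.23, power at 105 per group exceeds 99.99%. The stated 105 is not reproduced.

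**2. What 3.23 is.** The CI half-width is (9.56 + 3.37) / 2 = 6.465. Dividing by the t quantile gives the standard error of the difference:

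- 59 df (61 - 2): 6.465 / 2.001 = 3.231
- 53 df (31 + 24 - 2): 6.465 / 2.006 = 3.223

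Both agree with 3.23 to within 0.01. Had 3.23 been the SD, the half-width would have been 2.001 × 3.23 × √(1/33 + 1/28) = 1.66, or 1.76 with 31 and 24, so an interval of roughly 1.4 to 4.8.

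**3. The SD that the stated sizes need (80% power, exact t).**

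- 105 per group, 3.1 points: SD 7.98
- 91 per group, 3 points: SD 7.18

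The 182 chosen equals the Table 1 entry for SD 7 and difference 3. At SD 7, exact t needs 87 per group, and 91 per group gives 82% power.

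**4. The SD that the pilot interval implies.** SD = SE / √(1/n1 + 1/n2), with SE 3.23:

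- 33 and 28: 3.23 / 0.2569 = 12.57
- 31 and 24: 3.23 / 0.2719 = 11.88

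Both exceed the largest SD in Table 1.

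**5. Unadjusted power (exact t).** Expected completers: 108 × 0.8 = 86 per group.

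| SD | 86/group, 3 points | 91/group, 3 points | 105/group, 3 points | 105/group, 3.1 points |
|---|---|---|---|---|
| 7 | 80% | 82% | 87% | 89% |
| 8 | 69% | 71% | 77% | 80% |
| 11.88 | 38% | 40% | 45% | 47% |
| 12.57 | 34% | 36% | 41% | 43% |

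**6. Difference detectable with 80% power.** The detectable standardised effect is 0.430 at 86 per group and 0.418 at 91. In RNLI points at 86 per group: 3.0 (SD 7), 3.4 (SD 8), 5.1 (SD 11.88), 5.4 (SD 12.57). At 91 per group: 2.9, 3.3, 5.0 and 5.2.

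**7. Effect of baseline adjustment.** The Analyses section includes baseline RNLI as a covariate. Assume equal variances at baseline and follow-up and a correlation r between them (r is not in the documents). The residual SD is then the change-score SD × √((1 + r)/2). For r from 0.3 to 0.7 and SDs of 11.88 to 12.57, power for 3 points at 91 per group is about 41% to 56%.

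**The case against.** The best defence is that 3.23 did no work. It would have given 19 per group, so the sizes must come from another SD. The chosen 182 traces to a tabulated SD of 7, under which the 80% claim for 3 points is arithmetically sound. That stands, and it rules out a tempting stronger reading: that the authors used a standard error as the SD and that true power is therefore 35-45%. Mislabelling 3.23 did not set the sample size, so it cannot by itself lower the power.

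The low figures are also conditional. They need the printed interval to be an unadjusted two-group comparison of pilot change scores, and the trial's SD to equal that of a single-site pilot. The estimates are described as modified in an unstated way, and the planned model adjusts for baseline. This stands too, though adjustment over the range assumed above does not bring power near 80%.

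A reader might further infer that the pilot refutes the feasibility of 3 points because its interval includes zero. It does not: the point estimate is 3.1 and the interval reaches 9.56. Nor do the documents show that a null result would be misread, since the Analyses section already commits to reporting mean differences with 95% CIs.

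What the defence does not remove is that the text attributes 105 per group to an SD that cannot produce it. The SD of about 7 or 8 that would produce the sizes is neither stated as the planning value nor sourced, and it disagrees with the only pilot variability printed.

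**Conclusion.** The paragraph is wrong as written. Two parts need no assumption about how the trial will turn out: the stated inputs give 19 per group rather than 105, and 3.23 cannot be the within-group SD behind the printed interval. That 3.23 is the standard error of the pilot difference is an inference, but a strong one, since the interval returns 3.22 to 3.23.

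The true power is not established. For 3 points at 91 per group it runs from about 36-40% (SD 11.9-12.6, unadjusted) to about 71-82% (SD 7-8). At 86 completers the corresponding ranges are 34-38% and 69-80%. The documents do not show which SD applies. They do show that the 80% claim currently has no stated basis, and that the pilot interval points to the unfavourable end.

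**What to change.** 1. Correct the description of 3.23. If it is the standard error of the pilot difference, say so.
2. State the SD of the RNLI change score actually used for 105 and for 91 per group, give its source, describe the modification of the pilot estimates, and reconcile the result with the interval of -3.37 to 9.56.
3. Restate the power for 3 points and the detectable difference at the expected 86 completers per group, over SDs from 7 to 12.6, with and without baseline adjustment. Keep the 80% statement only if the sourced SD supports it.
4. Keep enrolment at 216, and commit to interpreting the primary CI against the 3-point important difference.

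The cost is wording and a short recalculation from pilot data that the authors hold; no participants are added. The downside is that the stated power may become much less favourable.

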### Proposed subgroup analyses

We will also complete two subgroup analyses to address the following questions.Are there sex differences in the specified outcomes? We will use an interaction term sex × treatment group to complete this analysis.Are there differences in according to age in the specified outcomes? We will use an interaction term age (18–55 years) (56+ years) to complete this analysis.

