Subgroup analyses: sex differences in response to treatment; age group differences response to treatment	Sex differences response to treatment; age group differences response to treatment	Interaction term sex × treatment group; interaction term age group × treatment group	Regression analysis with interaction test between each subgroup variable and treatment group evaluating the credibility of subgroup findings using previously published criteria
Sensitivity analyses: to evaluate the effect of group that adheres to treatment			Regression analysis

In all analyses, results will be expressed as estimate of effect, corresponding 95%, and associated *p* values

All tests will be one-sided using alpha = 0.05 level of significance in accordance with the non-inferiority hypotheses

*RNLI* Reintegration to Normal Living Index, *RAPA* Rapid Assessment of Physical Activity, *SPPB* Short Physical Performance Battery, *6MWT* 6-min walk test, *BBS* Berg Balance Scale, *EQ-5D-5L* European Quality of Life 5-Dimension Questionnaire, *BP* Blood pressure, *HR* Heart rate, *BMI* Body mass index, *HDL* High density lipoprotein, *LDL* Low density lipoprotein, *PAM* Patient activation measure, *CRF* Case report form

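### Subgroup analysis is given as a reason for n = 182, but 182 is a plain two-group size with no allowance for interaction tests

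*Protocol article*

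**What the plan says.** Under Sample size justification, the protocol article first sets a main-effect calculation of 105 per group (210), with "two-tailed type I error of 0.05; type II error of 80"%. The last figure evidently means 80% power, which the section states elsewhere. The inputs printed there are "the mean difference is 3.1 (95% confidence interval [CI] = -3.37–9.56") and "the common within-group standard deviation is 3.23".

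The next paragraph changes the number. It opens "To allow for subgroup analysis, and to control for factors of age and function, as well as balancing of the number of participants" between groups at the three sites, and continues "we chose a sample size of n = 182 (i.e. 91/group), which corresponds to a minimal clinically important difference of 3". It claims 80% power for a time-by-treatment interaction. It then moves to 216 on the basis of 30 per group per site and 20% dropout. No power is stated for any subgroup test.

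The only 182 in Table 1 is in the SD 7.0 row, which reads "7.0 1604 404 182 100". The columns are differences of 1.0 to 4.0, so 182 belongs to a difference of 3.0.

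Proposed subgroup analyses names a sex-by-treatment term and, for age, "We will use an interaction term age (18–55 years) (56+ years) to complete this analysis". Table 2, under Analyses, gives the method as "Regression analysis with interaction test between each subgroup variable and treatment group".

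**The concern.** A stated reason for a sample size tells the reader what the trial was built to do. Here subgroup analysis comes first among the reasons for 182, yet the number comes from a table of two-group sizes and is lower than the one already given for the main effect. Planning for interaction tests cannot make a trial smaller.

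What is at stake is how a null subgroup result is read. Someone told that the trial was sized for subgroup analysis may take a non-significant sex or age interaction as a sign that the programme works equally well in men and women, or in younger and older people. If the test would usually miss an interaction as large as the whole target effect, a null result says very little.

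**Working it through.** **Inputs.** Difference 3 and n = 91 per group (Sample size justification); SD 7.0 (inferred from the Table 1 cell that holds 182); two-sided 0.05; 1:1 allocation (Randomization). The share p in the smaller subgroup is my assumption, since the article gives none. So is an interaction of 3 points, chosen to equal the target difference.

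**1. Reproduce 182.** n per group = 2 × [7 × (1.960 + 0.842) / 3]² = 85.5, so 86 per group (172 in total); an exact t-test calculation gives 87 (174). The stated 182 is 8 to 10 higher. At 91 per group:

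- SE(main) = 7 × √(2/91) = 1.038
- power = Φ(3/1.038 − 1.960) = Φ(0.931) = 82% (82.0% by the t-test)

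So 182 is a slightly generous main-effect size. The α = 0.02, β = 0.05 printed under Table 1 would need 172 per group and does not produce it either.

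**2. Compare with the other main-effect size.** For a difference of 3.1, 105 per group gives 80% power at an SD of about 8. That total of 210 exceeds 182 by 28. Later in the section 182 becomes 216, but for sites and dropout.

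**3. Standard error of an interaction.** The interaction is the difference between two subgroup treatment effects. With 1:1 allocation within subgroups and a common SD:

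SE(int) = SE(main) / √(p(1 − p))

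The divisor is at most 0.5, so SE(int) is at least twice SE(main), whatever the SD. If main-effect power is 80%, the effect is 2.80 standard errors. An interaction of the same size is then at most 1.40 standard errors, with power Φ(1.40 − 1.96) = 29%. At 82% main-effect power the ceiling is 30%.

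**4. Numbers at SD 7.**

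- p = 0.5: SE(int) = 1.038/0.5 = 2.08; power for 3 points 30%; detectable at 80% power 2.80 × 2.08 = 5.8 points
- p = 0.2: SE(int) = 1.038/0.4 = 2.59; power 21%; detectable 2.80 × 2.59 = 7.3 points

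Intermediate splits give 29% (40/60) and 26% (30/70). Power of 80% for a 3-point interaction would need about 684 evaluable participants at 50/50 and about 1,070 at 20/80.

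**5. Sensitivity** (3-point interaction, 91 per group unless stated):

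| Assumption | 50/50 | 20/80 |
|---|---|---|
| SD 7, two-sided 0.05 | 30% | 21% |
| SD 8 (fits 105 per group) | 24% | 17% |
| SD 7, one-sided 0.05 (Table 2 footnote) | 42% | 31% |
| SD 7, all 216 analysed | 35% | 24% |
| SD 3.23 as printed | 88% | 71% |

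The last row cannot be the basis of the design. An SD of 3.23 needs only 19 per group for a difference of 3, or 18 for 3.1, so it yields neither 91 nor 105. The printed interval has half-width (9.56 + 3.37)/2 = 6.465, and half of that is about 3.23. The figure therefore looks like a standard error of the difference, though the article does not say so.

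**The case against.** The strongest reply is that the protocol never promises power for the subgroup tests. It says that the sample size was calculated for the primary outcomes, lists subgroups as one of three loose reasons, and attaches 80% power only to the time-by-treatment interaction. That is correct. A reader might infer that the article claims 80% power for sex and age and gets it wrong; it does not, and no stated subgroup figure is in error. What fails is the rationale.

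A reader might also take 30% for sex and 20% for age as properties of the trial. The documents do not support that. Neither split is given, SD 7 is inferred, and the 3-point interaction is a benchmark. That the 18–55 group will be small is likewise assumed; the article gives no age distribution and expects a wide age range.

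The planned model includes the baseline score, which may reduce the residual SD. At an assumed 6, interaction power with equal subgroups is about 39% while main-effect power rises to about 92%. The gap remains.

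Finally, effect estimates with 95% intervals are already planned, and Table 2 commits to judging subgroup findings against published credibility criteria. Both guard against careless subgroup claims. Neither makes 182 a size chosen for subgroups.

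**Conclusion.** The point holds in a limited form. The subgroup rationale for 182 is unsupported: the number is a two-group main-effect size, contains no allowance for interactions, and is below the section's own 210. That conclusion needs no assumption about splits.

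The size of the shortfall is conditional. If main-effect power is about 80%, an interaction as large as the main effect has at most about 30% power. With SD 7 and a two-sided 0.05 test, a 3-point interaction has about 30% at best and about 21% at 20/80, so it would be missed in roughly 70 to 80% of trials under those assumptions. SD 8 lowers the figures and the one-sided footnote raises them, to no more than 42%. Only the printed SD of 3.23 gives high power, and it is incompatible with both stated sample sizes.

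**What to change.** - In Sample size justification, remove subgroup analysis as a reason for n = 182, or state that the size is set for the main effect with no allowance for interactions. In the same edit, reconcile 182 with the 105 per group (210), since calling 182 the main-effect size without doing so would leave two competing figures.
- State that the sex and age interaction tests are exploratory, that power for a 3-point interaction is about 30% at best under SD 7 and lower with unequal groups, and that a non-significant interaction will not be read as equal benefit. Name the SD and the sidedness beside the figure.
- As a secondary improvement, test treatment by age with age continuous and keep 18–55 and 56+ for display. This adds a linearity assumption, which a spline can check. The gain depends on an age distribution that the article does not give.

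The cost is wording and, if the last item is adopted, one model term. No more participants are needed. The price is a more modest statement of what the subgroup analyses can show.
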